# Evaluating an intervention to improve the safety and experience of transitions from hospital to home for older people (*Your Care Needs You*): a protocol for a cluster randomised controlled trial and process evaluation

**DOI:** 10.1186/s13063-023-07716-z

**Published:** 2023-10-14

**Keywords:** Transitions of care, Discharge, Cluster randomised controlled trial, Hybrid interventions, Patient involvement, Older people, Study protocol, Readmission

## Abstract

**Background:**

Older patients often experience safety issues when transitioning from hospital to home. The ‘Your Care Needs You’ (YCNY) intervention aims to support older people to ‘know more’ and ‘do more’ whilst in hospital so that they are better prepared for managing at home.

**Methods:**

A multi-centre cluster randomised controlled trial (cRCT) will evaluate the effectiveness and cost-effectiveness of the YCNY intervention.

Forty acute hospital wards (clusters) in England from varying medical specialities will be randomised to deliver YCNY or care-as-usual on a 1:1 basis. The primary outcome will be unplanned hospital readmission rates within 30 days of discharge. This will be extracted from routinely collected data of at least 5440 patients (aged 75 years and older) discharged to their own homes during the 4- to 5-month YCNY intervention period. A nested cohort of up to 1000 patients will be recruited to the study to collect secondary outcomes via follow-up questionnaires at 5-, 30- and 90-day post-discharge. These will include measures of patient experience of transitions, patient-reported safety events, quality of life and healthcare resource use. Unplanned hospital readmission rates at 60 and 90 days of discharge will be collected from routine data.

A process evaluation (primarily interviews and observations with patients, carers and staff) will be conducted to understand the implementation of the intervention and the contextual factors that shape this, as well as the intervention’s underlying mechanisms of action. Fidelity of intervention delivery will also be assessed across all intervention wards.

**Discussion:**

This study will establish the effectiveness and cost-effectiveness of the YCNY intervention which aims to improve patient safety and experience for older people during transitions of care. The process evaluation will generate insights about how the YCNY intervention was implemented, what elements of the intervention work and for whom, and how to optimise its implementation so that it can be delivered with high fidelity in routine service contexts.

**Trial registration:**

UK Clinical Research Network Portfolio: 44559; ISTCRN: ISRCTN17062524. Registered on 11/02/2020.

**Supplementary Information:**

The online version contains supplementary material available at 10.1186/s13063-023-07716-z.

## Background

For older people and those with complex needs, the transitional period of moving from hospital to home poses various risks [1, 2]. As many as one in five patients experience an adverse event during this time; an estimated 62% of these could be prevented or ameliorated [3]. Over the last decade, emergency readmission rates have been increasing with around 30% of all readmissions estimated to be avoidable [4–7]. Older people have the highest rates of readmissions suggesting that this group have the greatest need for support to improve transitions of care [7].

A meta-analysis of 92 randomised controlled trials (RCTs) of interventions to improve transitional care for older people observed a significant reduction in hospital readmissions at multiple time points up to 12 months post discharge [8]. The interventions tended to be highly complex, adopting multiple and variable components, and commencing and ending at different time-points. Consequently, delineating which components are the active ingredients is challenging [9–11]. There is some suggestion however that interventions which seek to enhance patient capacity to ‘reliably access and enact’ post-discharge care [12, 13] or which emphasise patient education and promote self-management [14] are most likely to be effective.

Qualitative evidence increasingly shows that patients and their carers have a central role in supporting safe care throughout the care pathway [15–17]. Patient involvement in care *during* the hospital stay (through retaining knowledge and capability to undertake usual care activities) may be a key mechanism for enhancing patients’ capacity to ‘reach-in’ to the health care system enabling them to optimise their care [18]. However, patient involvement in hospital care is not intuitive [19, 20] and is unlikely to be enacted without intervention or support. The mechanism for doing this has not been fully explored.

To address this knowledge gap, the Partners At Care Transitions (PACT) programme of research evaluates how and whether greater involvement of older patients and their families during a hospital stay can improve patient experience and safety at transitions of care. The Your Care Needs You (YCNY) intervention aims to support older people to *know more* and *do more* whilst they are in hospital. By preparing people during their hospital admission, they will be better supported to manage their health when they get home [21].

The intervention comprises both fixed and flexible components that can be tailored to the context of each participating ward — a so-called hybrid intervention [22]. This aligns with recent research which suggests that interventions should be standardised by the function of a component, rather than standardising interventions according to the specific form that they take [23]. Our early work and feasibility cRCT identified that patients were positive about the intervention; however, without encouragement from staff, patients were unlikely to do more than read the information provided [24–27]. Based on these findings, we refined the intervention and implementation strategy and we now seek to assess the effectiveness and cost-effectiveness of the YCNY intervention.

## Methods

### Study aims and objectives

To assess the effectiveness and cost-effectiveness of the YCNY intervention compared to care-as-usual in reducing the rate of unplanned hospital readmissions in patients aged 75 years and over with embedded process evaluation.

#### Objectives

To assess the effectiveness of the YCNY intervention at reducing the rate of unplanned hospital readmissionsTo assess the effectiveness of the YCNY intervention at improving the quality and experience of transitions and quality of lifeTo assess the cost-effectiveness of the YCNY intervention compared to care–as-usualTo assess the fidelity of the intervention deliveryTo investigate the implementation of the intervention, exploring contextual factors that affect the way the intervention is used in practiceTo explore the mechanisms of action, specifically how YCNY is received and used by patients, carers and staff.

### Study design

A cluster RCT of the YCNY intervention versus care-as-usual in older people during the transition from hospital to home. Forty wards that routinely provide care for people aged 75 years and older, from up to 11 National Health Service (NHS) hospital Trusts in England will be randomly allocated to one of two arms: YCNY or care-as-usual (control). A process evaluation will also be conducted on a maximum of eight intervention wards to understand how the intervention is delivered, received, and used by staff and patients and how this is shaped by contextual factors.

The SPIRIT checklist [28], is available in Additional file 1.

### Setting

The cRCT will be conducted across NHS-funded, inpatient hospital wards that provide care for mostly older people and agree to participate in the trial. This may include older peoples’ medicine, intermediate care, respiratory medicine, orthopaedics, cardiology, surgical and stroke wards. Acute medical admission wards, and wards without regular medical input will be excluded.

Eligible patients will be 75 years and older, discharged to their own or a relative’s home, have stayed on a participating ward for at least one night, and be willing and able to provide informed consent. Where possible, informal carers will be recruited if patients lack capacity. Patients will be excluded if: they require an interpreter; are expected to be discharged to a nursing/care home or intermediate care/rehabilitation bed; are at end of life; live out of area; or have been admitted for psychiatric reasons (other than delirium or dementia).

### Randomisation

Wards will be randomly allocated in an equal allocation ratio (1:1) with 20 randomised to the Intervention and 20 to care-as-usual. Random allocation will be undertaken independently by the York Trials Unit (YTU) with minimisation using minimPy [29] and stratified by ward type (speciality), the percentage of patients over 75 years (split by ≤66% and >66%, based on the feasibility cRCT) and NHS trust.

### Patient population and sample size

Based on findings of similar interventions targeting readmission in a systematic review by Leppin and colleagues [12] and an underlying risk of readmissions of 18% for older patients (based on local hospital statistics), we anticipate an absolute difference in readmission at 30 days between control and intervention wards of between 4% and 6%. We therefore plan for a 4.5% reduction in readmissions at 30 days. Assuming 80% power, alpha = 0.05, intraclass correlation coefficient ) = 0.01, average cluster size = 140 (30–40 older people discharged per month from 40 wards for 5 months) and 10% attrition rate, 5440 participants are needed.

It would not be efficient to design the study to recruit and consent 5440 patients. Instead, we will use routinely collected data to explore readmission rates and include individual data collection of a nested cohort of participants within this larger sample. We will power the nested individual data collection cohort for our secondary outcome of quality of transitions. This will be measured by the Partners At Care Transitions Measure (PACT-M) [30] which produces an overall score between 0 and 67. Assuming a mean difference of 2.7 points, which equates to a reduction of around half an adverse event and a standard deviation of 9 (based on data from the feasibility cRCT), 170 patients per group are required (80% power, alpha = 0.05). Allowing for clustering this would increase to (assuming equal clusters of 25 patients and an ICC of 0.05) 374 patients per group. Allowing for 25% attrition (based on projected results from our feasibility study) we will recruit 500 patients per group (1000 total) which would require 40 clusters. We assume an ICC of 0.05 in the absence of published data indicating the most appropriate ICC for this setting and particular outcome.

### The Your Care Needs You (YCNY) intervention

#### Name of the intervention

The Your Care Needs You (YCNY) intervention was co-designed by patients, staff and researchers [27]. The intervention and implementation package were refined following a small formative evaluation [24] and a feasibility cRCT.(25;26) The structure and content of the intervention is described below using an adapted version of the TIDieR checklist [31].

#### Aims and underpinning programme theory

YCNY aims to improve the safety and experience of older patients as they transition from hospital back to their own homes. Our earlier work to model transitional care identified four key activities that patients hand over responsibility for, at the point of hospital admission, and then assume (to varying degrees) once they are discharged home [21]. These are managing their health and wellbeing, medications, daily activities, and escalating care needs.

The underpinning programme theory of YCNY posits that supporting patients to *know* and *do* more whilst they are in hospital, will help patients be better prepared for managing at home [21].

#### Intervention components

The intervention comprises three fixed patient-facing components.A patient booklet which makes explicit the opportunities for patients to be more actively involved in their care whilst in hospital to support a safer transition home. The booklet is structured around the four key activities and supports them to ask staff questions.A short patient film based on real patients’ stories from our earlier qualitative work [19]. The film brings to life, and seeks to underline, our hypothesised links between playing an active role within hospital and better outcomes after discharge.A patient advice sheet which supports patients to navigate care after discharge and seek help if needed. This will be tailored at the ward level prior to implementation.

In addition, ward staff will consider how they currently support patient involvement with respect to the four key activities, and what else they can do to enhance this. The actions that the teams decide to undertake (the flexible staff-facing intervention components) will not be prescribed — they will be left to vary according to staff preferences, current activities/initiatives on the ward that already address the four key activities, and their patient population.

#### Site engagement and implementation

The intervention will be supplemented with, and supported by, an ‘implementation package’ informed by the barriers and facilitators to engagement that we have previously identified [19, 20, 24, 26] and the ‘Capabilities, Opportunities and Motivation’ Behaviour change (COM-B) model [32]. Initial engagement and set-up of the intervention will be facilitated by researchers although trusts will vary in the extent to which they want to lead on/have support for these set-up activities. The process will involve four key stages outlined in Fig. 1.

**Fig. 1 Fig1:**
[figure not shown]
YCNY set-up and implementation steps

Ward facilitators will receive training and support to help them: create a plan to set up and deliver the intervention; support other activities such as creating wider staff awareness; signpost to a YCNY training and education microsite; and encourage ward staff to interact with the intervention. Specifically, ward facilitators will:Motivate staff to engage with the intervention by promoting it as a way to consistently support good patient involvement and communication between staff, patients and carers. Suggestions such as helping patients to write down questions and reminding them (how and when) to use the booklet, responding to resultant queries and showing it to family members will be offered. The breadth of opportunities to use the booklet lends itself to a multidisciplinary team approach so motivating all staff to engage with the intervention in various ways will be key.Ensure that staff feel confident to introduce and engage with the booklet and film. A short script and some prompt cards are provided to help staff explain the booklet and film to patients. Videos on the microsite also demonstrate different ways the booklet could be introduced to patients.Ensuring that staff, patients and carers are prompted to engage with the intervention as a whole through the provision of posters tailored at the ward level.

Beyond this, integrating YCNY into the existing roles and responsibilities of team members is a known facilitating factor in the normalisation of an intervention into routine practice [29].

#### Delivery

Ward staff will be asked to deliver the intervention to all patients who are returning back to their own homes irrespective of age for the 4- to 5-month period during which patient recruitment takes place on the ward. This is to ensure that YCNY becomes usual care on the intervention wards. In the trial, however, only those meeting our eligibility criteria (i.e. adults aged 75 years and over and returning to their own or a relative’s home) will be recruited to follow-up. Recruitment will start on completion of the intervention embedding period. Patients who consent to the trial are likely to have been exposed to the intervention, although this will not be a condition of participation.

#### Control wards

Patients on control wards will receive care-as-usual — “The wide range of care that is provided in a community whether it is adequate or not, without a normative judgement” [33]. Care-as-usual will be provided by secondary care, primary care, community and social services and will be available to both intervention and control participants.

### Recruitment and consent

Recruitment will commence up to four weeks after the embedding period. Exact start dates for recruitment will vary by Trust and ward. Recruitment will last a minimum of between four and five months on each ward.

#### Screening and identification

To recruit the nested sample of 1000 patients, all patients aged 75 years and over will be screened for eligibility. Screening logs will record the numbers of eligible patients, key reasons for ineligibility, and recruitment/refusal rates. Screening data will be used to complete a CONSORT diagram for cluster trials.

#### Approach and consent

Potential participants will be approached as soon as possible after screening. Patients will be provided with a written information sheet and researchers will verbally discuss the study in further detail. All patients will have the opportunity to ask questions. Patients (and carers if needed) will then be given as much time as they need to decide whether or not to take part. If patients wish to take part, a written (or witnessed) consent form will be completed. With participant permission, the patients’ general practitioners (GPs) will be informed of their involvement in the study. This trial does not involve collecting biological specimens for storage.

#### Patients who lack capacity

A significant proportion of patients within this older population (75 years and over) are likely to lack capacity to make decisions about their care. These patients are often more vulnerable to safety incidents and poorer experiences during transitions of care [34]. It is important that this particular patient population is included in this study to promote inclusivity in research and enhance generalisability. Capacity will be assessed during the screening process and initial approach. If patients lack capacity, attempts will be made to identify and recruit an informal carer (e.g. family member or friend) who can act as a personal consultee for the patient. A written declaration will be gained from all participating consultees. If a personal consultee cannot be identified then the patient will not be recruited into the study.

For participants who lose capacity or feel unable to complete outcome measures at follow-up, but who are otherwise happy to remain in the study, researchers will seek to identify a carer who can act as a consultee and support data collection on behalf of the patient.

#### Withdrawal

Participants and consultees are free to withdraw from the study at any point, without needing to provide a reason for their withdrawal. However, the reason for withdrawal will be recorded if provided.

During the study, follow-up data will be collected at three time points post-discharge. Researchers will make up to four attempts to contact the participant at each time point. Failure to make contact will be recorded as missing data and the participant will be contacted again at the next scheduled follow-up. Participants will only be withdrawn from the study if they or their consultee request it, the patient is deceased, or they are lost to follow-up, i.e. no longer contactable.

### Outcomes

The *primary outcome measure* (*N*=5440) is unplanned hospital readmission rates at 30 days post-discharge. It will be assessed using routine data recording the dates of all unplanned hospital readmissions up to 30 days post-discharge from the participant’s index admission.

*Secondary outcome measures* are listed below with further details available in Supplementary file 1:Patient At Care Transitions Measure (PACT–M) [30]Care Transitions Measure 3 items (CTM-3) [35]Questions regarding post-hospital syndrome [36]EuroQol 5-Dimension Health Questionnaire (5 levels) (EQ5D-5L) and Proxy EQ5D-5L [37]Healthcare Resource Use [38]Questions regarding exposure to and utility of the interventionUnplanned hospital readmissions at 60 and 90 days.

Permission to obtain unplanned hospital readmissions data from non-individually consented patients was provided through the United Kingdom Confidentiality Advisory Group (21/CAG/005). Patients will be able to opt out of this process through the provision of an information leaflet on the wards that details the contact details for the research team.

### Other data collected

Routinely collected data will also be used to identify length of stay of the index admission (an indicator of exposure to intervention), ward moves (an indication of potential contamination, to be gathered for consented patients only), length of stay of all unplanned hospital readmissions (for cost-effectiveness analysis), length of time to each unplanned readmission, age at index admission, gender and death within 30, 60 or 90 days after discharge from the index stay.

Data will also be collected to assess the fidelity of intervention delivery using a fidelity ‘grid’ developed as part of our trial feasibility study [26]. Fidelity will be measured across a range of areas including adherence (content, coverage, frequency, and duration) and relevant moderators such as participant (staff and patient) engagement, quality of delivery, and context [39]. A range of data collection methods will be utilised to assess the fidelity of the intervention, including ward-level observations undertaken by local research nurses, checks on intervention materials given out by wards and their usage, and discussions with ward managers and ward facilitators at the end of recruitment. Fidelity information will also be collected from patients during the follow-up questionnaires. This data will be used in a Complier Average Causal Effect analysis [40]. A total score will be produced by summing scores for the six criteria and will provide a basis for assessing the impact of non-adherence on treatment effect estimates.

### Data collection

The Schedule of Events table (Fig. 2) below outlines the assessments to be undertaken during this study. Assessments will either be administered by a member of the research team or self-completed with or without support e.g. through telephone assistance from a member of the research team or by recording participants’ answers for them on a postal questionnaire. Consultees will complete assessments for those who lack capacity.

**Fig. 2 Fig2:**
[figure not shown]
The schedule of enrolment, interventions, and assessments (as per Standard Protocol Items: Recommendations for Interventional Trials SPIRIT) [28]

### Blinding

Within this study it will not be possible to blind treatment allocation to ward or research staff who are involved in recruitment. The intervention will become usual care on the intervention wards and posters are used to communicate information about Your Care Needs You to patients, staff and visitors. Blinding of outcome assessment will be assured for the study team and data analysts except in cases where the researcher is required to conduct telephone follow-ups to obtain secondary outcome measures. In these rare cases, the researcher will have access to information in the data management system about the ward the patient was admitted to. It is possible that researchers will remember those wards that are designated as intervention wards and control wards, meaning that blinding may be compromised in these cases.

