### Follow-up assessments (see the “ Outcomes” section above)

Following discharge from hospital, we will follow up recruited participants on control and intervention at three time points:Time 1 — post discharge: data collection will occur ideally between 5 and 17 days but up to a maximum of 21 daysTime 2 — 30 days post discharge: data collection will occur ideally between 30 and 45 daysTime 3 — 90 days post discharge: data collection will occur ideally between 90 and 105 days

At the point of recruitment, all participants will be advised that they will receive a questionnaire in the post and may receive a telephone call a few days later (as a reminder, to check receipt of the questionnaire or to offer support to complete). For participants who do not return questionnaires, a reminder will be sent out in the post and following this, one more reminder phone call will be made totalling up to four attempts to contact participants at each follow-up. Where contact is not made this will be recorded as missing data. Subsequent follow-ups will be initiated as planned. Researchers will not contact patients who have died since discharge.

If a patient loses capacity during the trial and therefore cannot complete the outcome measures, recruitment procedures will be followed to identify a personal consultee. Follow-up data will only be collected about participants who have lost capacity if the appropriate consent is in place. Participants will be given an unconditional £5 voucher at each follow-up time point.

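### The protocol relies on unblinded telephone follow-up being rare, but its own procedures offer researcher help to every participant, with no figure and no caller safeguard

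*Protocol article*

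**What the plan says.** The Blinding section of the protocol article states: "Blinding of outcome assessment will be assured for the study team and data analysts except in cases". The exception is telephone follow-up made to obtain secondary outcomes. On those calls it says: "In these rare cases, the researcher will have access to information in the data management system about the ward the patient was admitted to". It then admits the consequence: "It is possible that researchers will remember those wards that are designated as intervention wards and control wards", so that blinding may be lost for those patients.

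Two other sections describe how the questionnaires are collected. Under Data collection: "Assessments will either be administered by a member of the research team or self-completed with or without support". The support is illustrated as "through telephone assistance from a member of the research team or by recording participants’ answers for them on a postal questionnaire". Under Follow-up assessments, every participant is told at recruitment that they will be sent a questionnaire and "may receive a telephone call a few days later (as a reminder, to check receipt of the questionnaire or to offer support to complete". Those who do not return it get a postal reminder, after which "one more reminder phone call will be made totalling up to four attempts to contact participants at each follow-up". There are three follow-ups.

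The primary outcome has a different source: "It will be assessed using routine data recording the dates of all unplanned hospital readmissions". The abstract says that readmissions at 60 and 90 days also come from routine data.

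**The concern.** The assurance of blinding depends on one word. If researchers rarely collect questionnaire answers by telephone, their knowledge of the ward can do little harm. If they often do, many scores are taken by someone who can see the ward and may know the arm. The article puts no number on *rare*, and its follow-up procedures offer help to everyone, three times over, in a cohort aged 75 and older.

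The outcomes exposed are those a researcher helps to complete. PACT-M matters most, because the nested cohort of 1000 is sized on it and it records the patient's own account of the transition. EQ5D-5L feeds the cost-effectiveness analysis. If a caller's tone or prompting differs by arm, the arm difference shifts, and a larger sample does not correct that. The article describes no step that keeps ward or allocation from the caller.

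**Working it through.** **The sections side by side**

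| Question | Blinding section | Data collection and Follow-up assessments |
|---|---|---|
| How common is researcher-assisted completion? | Rare; no figure | One of the listed modes; help may be offered to any participant at each of three follow-ups; no figure |
| Can the caller see the ward? | Yes | Not addressed |
| Is anything done to mask callers? | Nothing described | Nothing described |

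These statements do not strictly contradict each other, since an offer of help can be made to all and taken up by few. But nothing in the procedures supports *rare*, and nothing limits the consequence if it proves wrong.

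**The plan's own figure.** Inputs from Patient population and sample size: difference 2.7, SD 9, 80% power, alpha 0.05 (two-sided assumed), clusters of 25, ICC 0.05, attrition 25%.

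- Per group before clustering: 2 × (1.96 + 0.8416)² × 9² / 2.7² = 174.4, so 175 (stated 170, within 3%).
- Design effect: 1 + (25 − 1) × 0.05 = 2.2. Then 170 × 2.2 = 374, as stated.
- Attrition: 374 / 0.75 = 498.7, so 499 (stated 500).
- Power at 374 / 2.2 = 170 effective per group: 79.0% (stated 80%).

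The sample size reproduces to within rounding and is not in dispute.

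**Illustration of the bias.** The documents give neither the share f of PACT-M scores taken by an unblinded caller nor the shift b that this adds to the arm difference among those scores. Both are assumptions. The overall shift is s = f × b. The standard error of the arm difference is 9 × √(2/170) = 0.976. With no true effect, the two-sided false-positive rate is 1 − Φ(1.96 − s/0.976) + Φ(−1.96 − s/0.976).

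| f (assumed) | b (assumed) | s = f × b | s / 2.7 | False-positive rate |
|---|---|---|---|---|
| 5% | 1 point | 0.05 | 2% | 5.0% |
| 25% | 1 point | 0.25 | 9% | 5.8% |
| 50% | 1 point | 0.50 | 19% | 8.1% |
| 50% | 2 points | 1.00 | 37% | 17.6% |

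The first row is what *rare* would mean; the last is what common use with a sizeable shift would mean. The documents do not say which applies.

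**The case against.** The strongest reply is that the protocol already declares this limitation. It states the exception, says the caller can see the ward, and concedes that blinding may be compromised. That stands: the article does not claim fully blind collection. What disclosure does not supply is support for *rare*, or any measure to protect the affected scores.

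Second, a call is not an outcome assessment. Participants only may be called, and a reminder or a check that the form arrived collects nothing. The Data collection section also covers all assessments, including the baseline EQ5D-5L, so listing researcher administration there does not show that it is common at follow-up. This stands too, and is why the telephone share must be treated as unknown.

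A reader might infer that blind collection fails for the secondary outcomes as a whole and that only the primary outcome is safe. The documents do not support that. A self-completed postal questionnaire has no caller, analysts are stated to be blinded, and readmissions at 60 and 90 days are secondary outcomes from routine data. A reader might also infer that callers had set up the intervention on the same wards. Site engagement and implementation says that researchers facilitate set-up, but nowhere does the article say that the same individuals make follow-up calls. Nor does it give the order of the intervention-exposure questions, so they may already come last.

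Finally, patients who have seen the posters or booklet may reveal their arm whatever the screen shows. Masking is therefore a partial remedy, though still a useful one. A sensitivity analysis by mode may properly sit in the separate statistical analysis plan; its absence from the article is not the criticism here.

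**Conclusion.** The point holds in a limited form. The word *rare* is unsupported by the follow-up procedures, callers can see the ward, and no safeguard is described. Blinding cannot be relied on for PACT-M, CTM-3, the post-hospital syndrome questions, EQ5D-5L and resource use where a researcher helps to collect them.

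The size of any bias cannot be stated from the documents. It runs from negligible (0.05 points, 2% of 2.7) to material (1.0 point, 37% of 2.7) across assumed shares of 5% to 50% and assumed shifts of 1 to 2 points. These figures show what depends on the missing proportion; they are not estimates. The readmission outcomes, including the primary, are unaffected. This is an inexpensive improvement to the nested cohort, not a threat to the main result.

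**What to change.** - Mask ward and allocation on the follow-up screen that callers use. This needs a database permission. The cost is that callers can no longer use the ward name as a memory prompt.
- Where existing staffing allows, have calls made by researchers who were not involved in that ward's set-up or recruitment.
- Place the intervention-exposure questions after the outcome measures, if they are not already there.
- Record the mode of completion for each questionnaire (self-completed, telephone-assisted, researcher-administered), report it by arm, and add a sensitivity analysis by mode. This costs one extra field and a short analysis.
- In the Blinding section, replace *rare* with the expected or observed proportion and state any safeguard in use.

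Masking reduces the risk but does not remove it, since patients may disclose their allocation. Trial status gives May 2023 as the expected end of post-discharge data collection. If collection is complete, what remains is to correct the wording with the observed proportion and, where mode was recorded, to report it by arm with the sensitivity analysis.
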